### Sensitivity analysis

*Exclude patients who underwent neurosurgical haemorrhage evacuation after randomisation:* The blinded data shows that after randomisation 14% of patients had neurosurgery before undergoing the first rated post-randomisation scan. In these cases, it is difficult to use the post-randomisation and post-neurosurgery scan to estimate the treatment effect because any change seen in intracranial haemorrhage expansion or infarction could be due to the effect of tranexamic acid or neurosurgery. The inclusion of these patients in the primary analysis may dilute any treatment effect towards the null. Therefore, we will conduct a sensitivity analysis excluding patients who underwent neurosurgery before a post-randomisation scan was done.

We hypothesise that patients who receive tranexamic acid may have less blood on a post-randomisation and post-neurosurgery scan compared with patients who receive placebo. We will express the effect of tranexamic acid on the total volume of intracranial haemorrhage measured on a post-randomisation and post-neurosurgery scan using a linear mixed model as above. If the patient has been scanned pre-randomisation (and pre-neurosurgery), we will include the pre-randomisation bleeding volume as a variable in the linear mixed model as above. To improve the precision of the effect estimate, we will extend this model to include each covariate and its interaction with bleeding volume: time from injury to scans, time from neurosurgery to scan, GCS, age and systolic blood pressure.

We will conduct a survival analysis using the time from randomisation to neurosurgery. The time to neurosurgery will be compared between treatment arms using a log-rank test. Because the log-rank test will only indicate whether there is a significant difference between treatment arms in the time to neurosurgery, we will also conduct a Cox regression analysis to quantify any difference in the hazard of neurosurgery between arms.

*Subarachnoid haemorrhage*: We will express the effect of tranexamic acid on the size (small-medium, large) and spread (focal-multiple, diffuse) of subarachnoid haemorrhage between trial arms, using relative risks and 95% confidence intervals estimated using generalised linear models.

### Subgroup analyses

*Time from injury to randomisation:* Most intracranial bleeding occurs within hours of injury
^5,
25,
29,
30^. Subgroup analyses will examine whether the effect of tranexamic acid on intracranial haemorrhage is modified by the time from injury to randomisation (≤1 hour, >1 to 3 hours, >3 to 8 hours). If there is minimal haemorrhage expansion after 3 hours
^25^, we expect tranexamic acid will have a lesser effect in reducing haemorrhage expansion in this group compared to the groups treated within 3 hours. We will conduct a linear regression analysis with an interaction between treatment (tranexamic acid, placebo) and time to randomisation (≤1 hour, 1–3 hours, >3–8 hours) to examine whether the effect of tranexamic acid on intracranial haemorrhage volume varies according to the time from injury to randomisation.

There may be an increase in the frequency of cerebral infarction with tranexamic acid in those treated after 3 hours of injury compared to those treated within 3 hours of injury
^15^. We will use relative risks and 95% confidence intervals estimated using generalised linear models to examine whether the effect of tranexamic acid on cerebral infarction varies within subgroups of time from injury to randomisation (≤3 hours, >3 hours). However, given the lower prevalence of cerebral infarction compared to intracranial bleeding, it will be difficult to reliably examine the effect of tranexamic acid on cerebral infarction within time strata. We will examine whether tranexamic acid increases the risk of adverse events in an individual patient data meta-analysis of 15,000 patients with TBI or spontaneous intracerebral haemorrhage (published separately)
^31^.

*Types of haemorrhage*: We will conduct the linear mixed model analysis specified in the primary analysis section separately for subdural, epidural and intra-ventricular bleeds.

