### Primary outcome

The mean volume of intra-parenchymal bleeding will be compared between trial arms in patients randomised within three hours of injury, adjusting for prognostic covariates.

In the original IMBS protocol
^18^, we said the total volume of intracranial bleeding would be compared between treatment groups. Since publishing the protocol, we have collected blinded data from 1700 trial patients, which suggest that any effect of tranexamic acid on intracranial bleeding expansion may only be reliably detected in intra-parenchymal bleeds. Intra-parenchymal bleeds are less likely to be surgically evacuated compared to subdural and epidural bleeds, which are often larger and therefore substantially increase intracranial pressure and require urgent neurosurgical evacuation. Large subdural and epidural bleeds are easier to evacuate because they occur outside of the brain tissue, whereas intra-parenchymal bleeds often occur deep within the brain tissue so it is difficult to evacuate them without causing further harm. Therefore, we may not be able to reliably examine the effect of tranexamic acid on subdural and epidural bleed expansion given that large bleeds are often evacuated before we can examine any effect of tranexamic acid on them. Including bleeds that may not be affected by tranexamic acid in the primary outcome would dilute any effect of tranexamic acid on intracranial bleeding expansion to the null. Furthermore, when excluding patients who have undergone neurosurgery by the first rated post-randomisation scan, the proportional expansion of intra-parenchymal bleeding from pre- to post-randomisation is greater than for all other types of intracranial bleeding. Indeed, a recent randomised trial found a statistically significant reduction in intracerebral bleeding expansion with tranexamic acid
^24^. Finally, intra-parenchymal bleeds are often spherical in shape, so there is less measurement error with the ABC/2 method of volume estimation compared to subdural and epidural bleeds, which have concave and convex shapes, respectively. For these reasons, the primary outcome will examine the effect of tranexamic acid on the total volume of intra-parenchymal bleeding.

In the original IBMS protocol

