The blinded data indicates that pre-randomisation and post-randomisation bleeding volumes are positively skewed. Because bleeding volumes are skewed, this data will be log transformed before entered into the linear mixed model. The anti-log of the treatment effect estimate and its corresponding 95% CIs will be presented to aid interpretation. The treatment effect estimates will provide an estimate of the relative increase or decrease in haemorrhage volume with tranexamic acid.

In the original protocol, we planned to analyse the primary outcome using ANCOVA. Since publishing the protocol, we learnt that less than 50% of patients were scanned both pre- and post-randomisation. Because the pre-randomisation mean bleeding volume of the observed data may be different from the true pre-randomisation mean bleeding volume, the estimates from the ANCOVA model may be biased. Compared to ANCOVA, linear mixed models are more powerful and typically less biased when there are missing data
^26^.

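### The time-to-randomisation subgroup analysis uses a linear regression on unqualified intracranial haemorrhage volume, departing without explanation from the primary log-scale mixed model of intra-parenchymal volume

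*SAP article*

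**What the plan says.** **Time subgroup, volume.** Under Subgroup analyses the SAP states: "We will conduct a linear regression analysis with an interaction between treatment (tranexamic acid, placebo) and time to randomisation". There are three strata (up to 1 hour, over 1 to 3 hours, over 3 to 8 hours), and the aim is to "examine whether the effect of tranexamic acid on intracranial haemorrhage volume varies according to the time from injury to randomisation". The paragraph does not mention the mixed model, the log scale, pre-randomisation volume, clinical covariates or a restriction to intra-parenchymal bleeds.

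**Time subgroup, infarction.** The same section plans relative risks from generalised linear models in two strata (up to and beyond 3 hours) to see whether the effect varies. It states no interaction term.

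**Primary outcome.** Of the original protocol the SAP says "we said the total volume of intracranial bleeding would be compared between treatment groups". It now says "the primary outcome will examine the effect of tranexamic acid on the total volume of intra-parenchymal bleeding". One reason given is "Including bleeds that may not be affected by tranexamic acid in the primary outcome would dilute any effect of tranexamic acid" towards the null, since large subdural and epidural bleeds are often evacuated before any effect can be seen.

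**Primary analysis.** "In the original protocol, we planned to analyse the primary outcome using ANCOVA". That was replaced by a linear mixed model of log volume with both scans as outcomes, because fewer than 50% of patients had both scans and "the estimates from the ANCOVA model may be biased".

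**Neighbouring analyses.** The subgroup item on types of haemorrhage applies the primary mixed model. Midline shift and post-neurosurgery volume (Secondary analyses) are also given mixed models.

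**The concern.** The time subgroup tests the idea behind restricting the primary outcome to 3 hours: that the effect on bleeding fades with delay. It is the only analysis in the SAP that formally tests whether the effect on volume differs by time. It is also the only treatment-effect analysis of a continuous outcome for which the SAP names a model other than the mixed model.

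Two things are at stake. First, the stratum results may not be comparable with the primary result, because neither outcome nor scale is fixed to match it. Second, either reading of the regression gives up something the mixed model was adopted to keep: patients with only one scan, or the information in the pre-randomisation scan. Interaction tests have low power to begin with, so avoidable loss of precision is unwelcome here. Leaving outcome, scale and adjustment open also allows choices to be made after the data are seen.

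**Working it through.** **1. Inputs (SAP, Sample size, unless noted).** Difference 28 − 24 = 4 ml; SD 28 ml; pre/post correlation 0.6; alpha 0.05 (two-sided assumed); 1:1 allocation (Introduction); 1700 patients, of whom 901 have both scans, leaving 799.

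**2. The SAP's own figures.** At 80% power (assumed; the SAP does not state it) the unadjusted total is 2 × 770 = 1540, against 1542 stated. Adjusted: 1542 × (1 − 0.6²) = 987, as stated. Power is 95.7% at 1700 (95% stated) and 76.4% at 901 (76% stated). The inputs therefore reproduce the plan.

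**3. Formulas for a main effect.** Let b be the number with both scans and p the number with only a post-randomisation scan, equally split between arms, with variances known and 4 × 28² = 3136.

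- Mixed model with a common pre-randomisation mean: variance = 3136 / (b/0.64 + p). Patients with only a pre-randomisation scan add nothing to the precision of the treatment effect.
- Complete-case regression with baseline (ANCOVA): variance = 3136 × 0.64 / b.
- Regression of post-randomisation volume without baseline: variance = 3136 / (b + p).

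**4. Results.** The SAP does not say how the 799 divide, so the range is shown, assuming each has exactly one scan.

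| The 799 unpaired patients | Mixed model: SE, power | ANCOVA: SE, power | No baseline: SE, power |
|---|---|---|---|
| all pre-scan only (p = 0) | 1.49, 76% | 1.49, 76% | 1.87, 57% |
| split evenly (p = 399) | 1.32, 86% | 1.49, 76% | 1.55, 73% |
| all post-scan only (p = 799) | 1.19, 92% | 1.49, 76% | 1.36, 84% |

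**5. Ratios to the mixed model.**

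- No baseline: 1.87/1.49 = 1.25 when p = 0, and 1.36/1.19 = 1.14 when p = 799. In information terms the loss is 1 − 1/1.25² = 36% down to 1 − 1/1.14² = 23%.
- ANCOVA: no loss when p = 0. When p = 799, the mixed model's SE is 1 − 1.19/1.49 = 20% smaller.

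The two losses belong to different models and cannot be added.

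**6. Bearing on the interaction.** These are main-effect figures. The same ratios apply to a contrast between strata only if the correlation and the pattern of missing scans are alike in each stratum.

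**7. Infarction.** Two stratum-specific relative risks with their intervals do not test a difference between them. The relevant quantity is their ratio, whose log has SE √(SE₁² + SE₂²), or equivalently an interaction term in one log-link model.

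**The case against.** The strongest reply is that much of this is silence rather than contradiction. The SAP does not say that the subgroup regression is untransformed, unadjusted or in ml; it could be meant on the log scale, and Between-centre effects adds site to the analyses. An article may also leave model detail to a fuller plan. That stands as far as it goes: a reader might infer a difference in ml with no adjustment, but the text does not say so. It does not explain why a different model class is named here when the next item in the same section points back to the mixed model.

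A reader might also infer that the subgroup goes back to total intracranial volume, an outcome the plan has rejected. The documents do not support that. The word total is absent from this paragraph, and the SAP elsewhere uses intracranial haemorrhage loosely when discussing the primary analysis (Sensitivity analysis). Total volume was dropped only as the primary outcome; it is kept for progressive bleeding and for patients who undergo evacuation. All intracranial bleeding is the more natural reading, but the defect is that the outcome is not pinned down.

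The stated reason for leaving ANCOVA concerns the observed pre-randomisation mean, so it applies only if baseline is adjusted for. This is accepted: the ANCOVA objection and the missing-baseline objection are alternatives. Without baseline, however, the regression cannot use the pre-randomisation scan to support the missing-at-random assumption that the SAP makes for its primary analysis.

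On infarction, a generalised linear model can carry an interaction, and the SAP itself concedes that infarction within time strata will be hard to examine reliably. So the point there is limited to the stated output.

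Finally, the primary and bleeding outcomes are already restricted to 3 hours, so this analysis supports the early-treatment hypothesis rather than carrying it alone.

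**Conclusion.** The concern holds in a limited form. The time subgroup names a linear regression on an outcome not specified as intra-parenchymal, and gives no reason for departing from the primary model. With baseline, it is the method the SAP replaced. Without baseline, its main-effect SE is about 1.14 to 1.25 times that of the mixed model.

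That size rests on a correlation of 0.6 taken from the sample-size calculation for overall intracranial bleeding in ml, which is not shown to hold for log intra-parenchymal volume, and on an assumed split of the unpaired scans. A flat 36% loss of information is only the upper end. Nor does excluding unpaired patients always cost precision: if they all lack the post-randomisation scan, ANCOVA and the mixed model have the same SE.

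For infarction, the point is only that separate relative risks do not by themselves show whether the effect varies. Neither the primary estimate nor its inference is affected.

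**What to change.** - Name the outcome of the time subgroup as intra-parenchymal volume. If all intracranial bleeding is intended, say so and give the reason.
- Fit the primary log-scale mixed model, with the same covariates and site, in all patients randomised up to 8 hours. Add time-stratum main effects by period (pre or post) and treatment-by-time-stratum terms for the post-randomisation volume. Keep pre-randomisation means equal between arms within each stratum.
- Report the ratio of volumes with its 95% CI in each stratum, and the interaction test. If the linear regression is kept, justify it and state its scale, baseline adjustment and covariates.
- For infarction, add the interaction term to the same generalised linear model and report the ratio of the two relative risks with its CI, noting the low power the SAP already concedes.

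The cost is a few lines of SAP wording and extra terms in code that will exist anyway; no new data are needed. Trial status dates unblinding to 31 May 2019, before this third version, so the change should be dated and labelled as made after unblinding.

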### Primary analysis

Linear mixed model
^26^ will be used to compare the mean change in intra-parenchymal haemorrhage volume from pre- to post-randomisation between treatment groups. The basic model includes pre- and post-randomisation volumes as correlated outcomes with mean post-randomisation volumes allowed to differ by treatment group but mean pre-randomisation volumes constrained to be the same, and with variances of pre- and post-randomisation volumes allowed to differ. In the absence of missing data, this linear mixed model gives identical estimates of the treatment effect, and near identical standard errors to the more standard ANCOVA analysis. The advantage of the linear mixed model approach is that patients with missing pre- or post-randomisation scans can be included in the analysis, potentially reducing bias and increasing efficiency
^26^.

A linear regression analysis of the blinded data indicated that time from injury to CT scan, GCS, age and systolic blood pressure are significantly predictive of the pre- and post-randomisation bleeding volumes (p<0.05). These covariates and the stratification factor (hospital site)
^27^ will be included in the analysis to improve the precision of the effect estimate. The main effect of site (which is treated as fixed) is accounted for in the model. Because we have relatively few centres (n=14) compared to the number of patients (n= ≈1750), we expect any loss in efficiency from this method (compared to the random centre effects method) to be minimal. The linear mixed model described above will include an interaction between each covariate and whether bleeding volume was measured before and/or after randomisation. This gives treatment effect estimates that are identical to those from the standard ANCOVA model in the absence of missing data. We expect the covariates to affect bleeding volumes in different ways (e.g. older people are likely to have larger bleeds at baseline, more severely unconscious people (low GCS) are likely to have larger bleeds at baseline). In line with the CONSORT guidelines
^28^, we will also report the results from the linear mixed model without covariate adjustment to facilitate synthesis and comparability with other trials that may not include the same covariates.

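### The treatment-by-time test on bleeding is specified as a linear regression on intracranial haemorrhage volume, not as the primary mixed model on log intra-parenchymal volume, and no reason is given

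*SAP article*

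**What the plan says.** Under Subgroup analyses, Time from injury to randomisation, the SAP article plans: "We will conduct a linear regression analysis with an interaction between treatment (tranexamic acid, placebo) and time to randomisation", with three groups (up to 1 hour, over 1 to 3 hours, over 3 to 8 hours). Its purpose is "to examine whether the effect of tranexamic acid on intracranial haemorrhage volume varies according to the time from injury to randomisation".

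The primary analysis is specified differently:

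- **Model and outcome** (Primary analysis): a linear mixed model "will be used to compare the mean change in intra-parenchymal haemorrhage volume from pre- to post-randomisation between treatment groups", with pre- and post-randomisation volumes as correlated outcomes, a common pre-randomisation mean, covariates and site.
- **Scale** (Primary analysis): "Because bleeding volumes are skewed, this data will be log transformed before entered into the linear mixed model".
- **Reason for the model** (Primary analysis): "Compared to ANCOVA, linear mixed models are more powerful and typically less biased when there are missing data".
- **Reason for the outcome** (Primary outcome): blinded data suggested that "any effect of tranexamic acid on intracranial bleeding expansion may only be reliably detected in intra-parenchymal bleeds".

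The item that follows the time subgroup returns to that model: "We will conduct the linear mixed model analysis specified in the primary analysis section separately for subdural, epidural and intra-ventricular bleeds".

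**The concern.** The plan restricts its primary outcome to patients randomised within 3 hours on the premise that later treatment has little effect on bleeding. The time subgroup is where the trial tests that premise on its own bleeding data. Yet the sentence departs from the primary analysis in model and outcome without explanation, and is silent on scale, baseline volume and covariates.

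Three things are at stake:

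- A regression of post-randomisation volume either keeps only patients with both scans or forgoes baseline volume, unless values are imputed. Reliance on complete pairs is what the plan gave as its reason for leaving ANCOVA.
- Interaction depends on scale. A treatment that cuts volume by the same percentage in every time group gives a smaller ml difference wherever volumes are smaller.
- If outcome and scale differ from the primary analysis, the interaction does not show whether the primary effect varies with time.

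**Working it through.** **1. Is the sentence shorthand for the primary model?** Probably not.

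- Under Primary analysis, the plan uses the term linear regression for a separate exploratory fit to blinded data, and linear mixed model for the planned comparison.
- Under Secondary analyses, the models for millimetres of midline shift and for post-neurosurgery volume both refer back to the mixed model. So does the bleed-type subgroup. The time interaction has no such reference.
- The time subgroup includes patients randomised after 3 hours, who are outside the primary population, so primary settings do not carry over by default.

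**2. The plan's own figures reproduce.** From Sample size: 24 v 28 ml (difference 4 ml, ratio 24/28 = 0.857), SD 28 ml, correlation 0.6, alpha 0.05 (two-sided assumed), with 80% power assumed.

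- The unadjusted total is 1540 by the normal formula and 1542 by the t-based one (stated 1542).
- Adjusted: 1542 × (1 − 0.36) = 986.9 (stated 987).
- Adjusted SD = 28 × √(1 − 0.36) = 22.4 ml. Power is 95.7% at 1700 (stated 95%) and 76.4% at 901 (stated 76%).

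The plan states no power for the interaction.

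**3. Interaction power, two groups.** SE = SD × √(4/(N·f) + 4/(N·(1 − f))), where f is the share randomised within 3 hours. Take N = 901, f = 0.7 (assumed), the planned effect early and none late. The root term is √(4/630.7 + 4/270.3) = 0.1454.

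For the log scale, assume lognormal volumes with mean and SD both 28 ml. Then log SD = √(ln 2) = 0.833, log correlation = ln(1.6)/ln 2 = 0.678, adjusted log SD = 0.833 × √(1 − 0.678²) = 0.612, and effect = ln(28/24) = 0.154.

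| Reading | SD | SE | Effect/SE | Power |
|---|---|---|---|---|
| Log, with baseline | 0.612 | 0.0890 | 1.73 | 41% |
| Log, no baseline | 0.833 | 0.1211 | 1.27 | 25% |
| Raw ml, with baseline | 22.4 | 3.257 | 1.23 | 23% |
| Raw ml, no baseline | 28 | 4.071 | 0.98 | 17% |

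The two raw rows use only the plan's SD and correlation plus the assumed f. Dropping baseline there costs about 30% of the power (23% to 17%).

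**4. Three groups with missing scans.** This is a simulation of 2,000 runs with a 2-df Wald test at 5%. Assumed: 1700 patients; time shares 20/50/30%; 53% with both scans, 17% post only, 30% pre only, missing completely at random; lognormal volumes without zeros. Regressions with baseline use complete pairs, and those without use everyone with a post-randomisation scan. The mixed model was fitted with its covariance taken as known. The first scenario has a 15% reduction up to 3 hours and none later; the second has 30%, 15% and 0% by group.

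| Model | 15/15/0% | Relative loss | 30/15/0% |
|---|---|---|---|
| Log mixed model | 35% | – | 83% |
| Log regression, with baseline | 33% | 6% | 76% |
| Log regression, no baseline | 23% | 35% | 62% |
| Raw ml, with baseline | 20% | 43% | 42% |
| Raw ml, no baseline | 16% | 54% | 38% |

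Relative loss is 1 − power/35.25%, using unrounded powers. For the last row, 1 − 16.05/35.25 = 54%.

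**5. Scale effect.** Give every time group the same ratio of 0.857, so there is no effect modification on the ratio scale. The ml difference is then the placebo mean × 4/28.

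| Assumed placebo means (ml) | ml differences | Raw-ml rejection | Log mixed model |
|---|---|---|---|
| 28 / 28 / 28 | 4.0 / 4.0 / 4.0 | about 5% | about 5% |
| 35 / 28 / 20 | 5.0 / 4.0 / 2.9 | about 9% | 5% |
| 40 / 28 / 14 | 5.7 / 4.0 / 2.0 | 13–17% | about 5% |

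**The case against.** The sentence is brief, in a journal article, about a subgroup. A reader might infer from it that the test runs on total volume, in raw ml, without baseline. The document states none of these. It says intracranial haemorrhage volume, whereas the neurosurgery analysis says total explicitly. The log transform is worded for the mixed model, but nothing says it is abandoned elsewhere. Baseline could be imputed. That objection stands, and it is why the power loss has to be given as a range.

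A reader might also infer that the scale effect would produce the plan's predicted pattern of less benefit after 3 hours. The plan reports that time from injury to CT scan predicts volume. It gives neither direction nor size, and that is not time to randomisation. If later patients had larger volumes, the effect would run the other way.

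Nor is the wider patient set a defect, since any test across 3 hours must include later patients.

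The plan also says, under Secondary outcomes, that results for patients treated after 3 hours will be presented separately. That allows early and late estimates of the primary outcome to be set side by side, but it states no interaction test and so does not cure the mismatch.

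Finally, even the primary model has only about 35% power for the interaction under the planned 15% effect, so the change would not make the test reliable. This bears on severity, not on whether the text should be reconciled.

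**Conclusion.** The mismatch is real. The time interaction is assigned a model and an outcome that depart from the primary analysis, against the plan's own reasoning on dilution, skew and missing scans, and without a reason. Scale and baseline handling are left open in a plan meant to guard against data-dependent choices.

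The stronger claim, that the test loses half its power, is not supported as a single figure. It needs both raw ml and no baseline. The change that is actually in the text, mixed model to regression, costs only about 6% if logs and baseline are kept (8% under the steeper gradient: 1 − 76.25/82.7). The scale-driven interaction is possible only if raw ml is used and mean volume differs by time.

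These sizes rest on the assumed lognormal shape, time shares, missingness split and placebo means by group. They also rest on a 28 ml mean and SD that the plan set for intracranial bleeding as a whole, not for intra-parenchymal volume. Dilution from other bleed types is not quantified.

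Severity is moderate: a subgroup analysis, with the primary estimate and test unaffected and interaction power low under any model.

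**What to change.** Replace the linear regression sentence with the primary specification:

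- the constrained linear mixed model on log intra-parenchymal volume, with the same covariates and site;
- fitted to all patients randomised within 8 hours, with the primary result itself still restricted to 3 hours;
- with time-group terms added, and a treatment-by-time-group interaction on the post-randomisation mean.

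Report the treatment ratio with its 95% CI in each time group and the interaction test. All-type intracranial volume can be shown as supportive, in the same model. If a separate regression is preferred, give the reason and state its outcome, scale, baseline handling and covariates.

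The cost is one sentence of SAP wording and a few extra terms in a model that is already planned. No new data are needed. As the SAP records that the trials have been unblinded, a later revision should be dated and labelled as made after unblinding.
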